**Study Population and Sample Collection**

A total of 36 healthy human volunteers (males and females), aged between 3 and 65 years and residing in Abuja, North Central Nigeria, will be recruited for this study. Eligible participants will enter a two-week monitoring phase to ensure compliance with exclusion criteria, verified through a daily online 24-hour food and drug recall questionnaire. Participants will then be assigned to Kunun aya, Kunun zaki, or control group (no intervention) by chance as they come, with 12 participants per group. Participants will supplement their habitual diet with 500 mL daily of the assigned beverage for two weeks, followed by a two-week washout phase.

Fecal samples will be self-collected by participants across three phases: prior to beverage consumption (baseline), after two weeks of beverage consumption, and at two weeks post-intervention (washout phase). Samples will be prepared according to the method described by Nsubuga et al. (2004). DNA will be extracted from fecal samples using the DNA Stool Mini Kit (Qiagen, USA) according to the manufacturer's instructions and stored at −20°C.

**Expected Outcome:** At the end of this research it is expected that there will be significant changes in the gut resistome composition of participants following consumption of the local drinks. Specifically, we expect to observe changes in the abundance and diversity of antimicrobial resistance genes, with potential decreases in clinically relevant ARG classes through competitive exclusion mechanisms and modulation of the gut microbial community structure.

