### Eligibility Criteria

### Inclusion criteria

Healthy individuals aged between 3 and 65 years, good general health, and a signed consent form (or assent with parental consent for minors).

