### Exclusion criteria

Engaging in any of these during 2 weeks prior to the first sample collection; antibiotic use, intentional intake of probiotic or prebiotic products, presence of gastrointestinal disorders such as diarrhea, inflammatory bowel disease, or irritable bowel syndrome, pregnancy or breastfeeding, alcoholism and drug addiction. For the entire 6 weeks this research will last for, participants will be required to report their daily food and drug intake using an individualised web app developed for this purpose.

Interventions and Comparator

**Intervention 1 - Kunun Zaki:** Participants will consume 500 mL of Kunun Zaki daily for 2 weeks. Kunun Zaki is a traditional Nigerian fermented beverage made from millet or sorghum, supplemented with ginger and cloves as spices.

**Intervention 2 - Kunun Aya:** Participants will consume 500 mL of Kunun Aya daily for 2 weeks. Kunun Aya is a traditional Nigerian fermented beverage made from tiger nuts, prepared through similar fermentation processes as Kunun Zaki.

**Control:** Participants in the control group will maintain their habitual diet without any intervention beverage for the 2-week period.

All participants will be instructed to maintain their usual dietary habits aside from the intervention beverage. Interventions will be delivered by study personnel who will ensure participants receive fresh beverages daily. Adherence will be monitored through daily self-reported logs via the web-based food diary.

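### The eligibility criteria do not exclude people with a known allergy or intolerance to the beverage ingredients, although the drink is assigned by chance and children from age 3 may enrol

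*Protocol*

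**What the plan says.** The Protocol's Inclusion criteria consist of one sentence: "Healthy individuals aged between 3 and 65 years, good general health, and a signed consent form (or assent with parental consent for minors").

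The Exclusion criteria open with a time window, "Engaging in any of these during 2 weeks prior to the first sample collection". They then list recently taken antibiotics, "intentional intake of probiotic or prebiotic products, presence of gastrointestinal disorders such as diarrhea, inflammatory bowel disease, or irritable bowel syndrome, pregnancy or breastfeeding", and alcohol or drug dependence. Nothing else is excluded.

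Under the same heading the Protocol describes the drinks. Kunun Zaki is "made from millet or sorghum, supplemented with ginger and cloves as spices". For the other drink it says "Kunun Aya is a traditional Nigerian fermented beverage made from tiger nuts". The dose is the same for both, for example "Participants will consume 500 mL of Kunun Aya daily for 2 weeks", and no smaller serving for children is stated.

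Under Study Population and Sample Collection, participants are "assigned to Kunun aya, Kunun zaki, or control group (no intervention) by chance as they come, with 12 participants per group". Before that they pass through a "two-week monitoring phase to ensure compliance with exclusion criteria, verified through a daily online 24-hour food and drug recall questionnaire". Frequency of interviews adds a first-contact questionnaire on suitability, described as anonymous. Its items are not given.

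Two explicit safeguards concern symptoms. Secondary Outcomes lists gastrointestinal symptoms reported by participants, and adverse events. Ethical Consideration tells participants to report signs of food poisoning, which lead to treatment and to stopping the study for that person. It also refers to further precautions without naming them.

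**The concern.** This is a feeding study of two products with named ingredients, and the participant does not choose which drink to take. Someone who knows that they react to tiger nuts or ginger would normally avoid it. Here that person meets every stated criterion and can be assigned the drink. Children depend on someone asking the parent.

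What is at stake is participant safety. As written, the criteria give study staff no stated ground for turning away a volunteer with a known reaction before assignment. Eligibility belongs in the protocol, so this is not a detail that a statistical analysis plan would be expected to supply.

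**Working it through.** The Protocol gives no figure to reproduce on this point. The check is to take each provision that might screen out a person with a known reaction and ask whether, as worded, it does so.

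**Exposure.** Two of the three arms receive a beverage: 12 + 12 = 24 of 36 participants, at 500 mL a day for two weeks. The named ingredients are millet or sorghum, ginger and cloves (Kunun Zaki) and tiger nuts (Kunun Aya).

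**Criteria that name allergy, hypersensitivity or intolerance.** Inclusion criteria: 0. Exclusion criteria: 0. The rest of the Protocol does not mention the subject either.

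**Could another provision do the work?**

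1. *Good general health (Inclusion criteria).* A person with a food allergy who avoids the food can be in good health, so this is not a specific screen.
2. *The gastrointestinal clause (Exclusion criteria).* The list is worded for the two weeks before the first sample. A person who avoids the ingredient and has no symptoms in that window need not be caught, and an allergy need not show as a gastrointestinal disorder.
3. *The two-week monitoring phase (Study Population and Sample Collection).* It precedes exposure, but its stated purpose is to check the listed exclusion criteria by food and drug recall. It is not set up to check a criterion that is not listed, and a record of what was eaten does not show why something was avoided.
4. *The first-contact questionnaire (Frequency of interviews).* It also precedes exposure and concerns suitability. It is not stated to ask about allergy, and no listed criterion would require it to. Because it is described as anonymous, an answer could not readily be acted on for a given person.
5. *Assumed habitual use (Ethical Consideration).* The Protocol says participants are used to the drinks, but only to argue that contamination risk is limited. Neither set of criteria requires prior use, and being used to one drink does not show tolerance of the other.
6. *Symptom and adverse event reporting (Secondary Outcomes).* For a reaction to the drink, this operates after consumption.
7. *Report, treat and discontinue (Ethical Consideration).* This also operates after consumption and is worded for food poisoning.

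No provision, as stated, identifies a person with a known reaction before the first serving. Items 3 and 4 come at the right time but are not stated to cover the subject. Items 6 and 7 cover symptoms but come later.

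**The case against.** The strongest reply is that this is an omission and not a false statement, and that the places where allergy might be raised cannot be seen. The consent pages were removed before review and the questionnaire's items are not given. That limits the point to what the Protocol states, and nothing is claimed here about consent or ethics material. The reply does not remove the gap, because the eligibility list is set out in full and is what staff would apply.

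A second reply is that harm needs several further steps. The concern is a known reaction, no blinding is described, participation is voluntary, and the study means to mimic habitual consumption of local drinks. A volunteer or parent who knows of a reaction can speak up or decline. This stands, and it lowers the likelihood of harm. It does not replace a question asked before assignment.

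Four stronger readings are tempting, and the documents do not support them:

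- *Every safeguard acts only after exposure.* The monitoring phase and the questionnaire come first, and Ethical Consideration mentions further, unspecified precautions. The narrower statement is that the earlier steps are not stated to cover allergy.
- *An enrolled reactor has a one-in-three chance of exposure.* The ratio 12/36 only restates the allocation. For the grains it need not mean exposure at all: Kunun Zaki is made from millet or sorghum, so a person who reacts to one may be given the other.
- *The primary comparison is affected.* Nothing in the documents shows this.
- *The assurance of no risk in Ethical Consideration is part of the same fault.* That wording is a separate matter and lends this point no weight.

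**Conclusion.** The point holds as a minor participant-safety improvement. The Protocol sets out its eligibility list without an exclusion for known allergy or intolerance to the beverage ingredients, in a study that assigns the drink by chance and admits children from age 3. The stated steps before exposure do not fill the gap, and the explicit symptom safeguards follow consumption.

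Its size cannot be expressed as a number of participants, because the documents give no frequency of such reactions. The conclusion rests on the Protocol's wording alone and assumes that staff apply the criteria as listed. If the questionnaire already asks about allergy, the remaining need is to make the answer a stated exclusion and to ensure that it can be linked to the person.

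**What to change.** Make three changes to the Protocol:

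1. Add to the Exclusion criteria: known allergy or intolerance to millet, sorghum, ginger, cloves, tiger nuts or any other ingredient of either beverage. Place it outside the two-week window and apply it to all three arms, so that the groups are selected alike.
2. Ask the question at the existing first contact, before assignment, and ask the parent in the case of a minor. Record the answer in a form that can be linked to the participant, since the questionnaire is now described as anonymous.
3. In Ethical Consideration, extend the report, treat and discontinue instruction to suspected allergic or intolerance reactions.

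The cost is one criterion, one question and one edited sentence. No visits or samples are added, and the sample size, alpha and analysis are unchanged. The downside is that a few volunteers may be screened out and need replacing to reach 36.

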**Sample Size**

A sample size of 36 participants (12 per group) was determined based on feasibility considerations and previous microbiome intervention studies.

### Laboratoy Methods

### DNA Extraction

DNA will be extracted from fecal samples using the DNA Stool Mini Kit (Qiagen, USA) following the manufacturer's instructions. Extracted DNA will be quantified using a NanoDrop spectrophotometer and stored at −20°C until analysis.

### Antimicrobial Resistance Gene Detection

Target antimicrobial resistance genes will be detected using conventional PCR with specific primer sets for genes conferring resistance to beta-lactams (blaTEM, blaSHV, blaOXA), macrolides (ermB, ermC, mef(A/E)), tetracyclines (tetA, tetB, tetM), and aminoglycosides (aac(3)-II, aac(6')-Ib, aph(3')-IIIa). Multiplex PCR will be employed where feasible to detect multiple genes simultaneously. Both multiplex and singleplex PCR reactions will be conducted in 20 μL volumes containing Master mix, gene-specific primers, DNA template, and molecular-grade water. Cycling conditions will be optimized for each gene target. Positive controls and negative controls (molecular water) will be included in all PCR runs to validate results.

**Data Collection procedure**

Sample collection would be done according to the method described by Nsubuga et al., (2004). Participants will be given sample bottles to collect their faecal sample after proper tutelage on the collection procedure. Approximately 5g of participant's feces would be aseptically collected into a tube containing 30 ml of 97 % ethanol and allowed to stand for 24-36 h. The bolus formed afterwards will then be transferred to 50ml tubes containing silica gel beads topped with a kim wipe and then stored at room temperature.

### Frequency of interviews

Interviews will be in the form of questionnaires used to anonymously collect data on their suitability as participants. There will be no other interviews besides the first contact and the 24hr food and drug recall.

### Statement on invasive sampling

No invasive samples will be collected from the participants.

### Statistical methods for primary and secondary outcomes

ARG prevalence will be calculated for each group at baseline, post-intervention, and washout phases. Statistical comparisons between groups and across time points will be performed to determine the effect of beverage consumption on antimicrobial resistance gene patterns in the gut microbiota.

Statistical comparisons of ARG prevalence between groups will be conducted using appropriate parametric or non-parametric tests depending on data distribution. Significant differences in resistome composition will be determined using permutational ANOVA (PERMANOVA) at 95% Confidence Interval and 0.05α. Comparison of means will be done using an unpaired t-test and Tukey's multiple-comparisons test where appropriate.

ARGs will be categorized by resistance mechanism and antibiotic class to identify which categories are most affected by the intervention. Changes in clinically relevant resistance genes will be given particular attention in the analysis and interpretation of results.

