## Primary and Secondary Outcomes

### Primary Outcome

The primary outcome is the change in gut resistome composition, measured as the difference in total antimicrobial resistance gene (ARG) abundance and diversity between baseline and post-intervention timepoints (2 weeks). This will be quantified using ARG detection by PCR, with results analyzed at the conclusion of the 2-week intervention period. The primary endpoint compares ARG profiles between the intervention groups (Kunun Zaki and Kunun Aya) and the control group using permutational ANOVA (PERMANOVA) with alpha set at 0.05.

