### Secondary Outcomes

1. Prevalence changes of specific ARG classes (beta-lactam, macrolide, tetracycline, aminoglycoside resistance genes) measured at baseline, 2-week post-intervention, and 2-week washout periods.

2. Persistence of resistome changes during the washout phase (measured at 2 weeks post-intervention cessation) compared to baseline and intervention periods.

3. Identification of specific ARG signatures that appear or disappear following consumption of each fermented beverage.

4. Safety outcomes including participant-reported gastrointestinal symptoms and adverse events throughout the study duration.

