**Research Design**

This is a human intervention study with three arms (1:1:1 allocation ratio) designed to assess superiority of two fermented beverage interventions (Kunun Zaki and Kunun Aya) compared to a control group (no intervention) in modulating the gut resistome. The research follows a quasi-experimental design with participants assigned to different groups by chance to receive either *Kunun Zaki, Kunun Aya*, or no intervention for a 2-week period, followed by a 2-week washout phase. Sample collection occurs at baseline (pre-intervention), at the end of the 2-week intervention period, and at the end of the 2-week washout period.

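### Comparisons across time are planned on the same people, but the only tests named for means are unpaired t and Tukey, so before/after and persistence tests are too conservative

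*Protocol*

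**What the plan says.** The design is one of repeated measures. Research Design states: "Sample collection occurs at baseline (pre-intervention), at the end of the 2-week intervention period, and at the end of the 2-week washout period". Sample Size gives 12 people per arm and rests that number on feasibility and earlier studies.

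Several aims are within-person. The Objective of the study compares the resistome before, during and after consumption. The Primary Outcome is a change from baseline to two weeks, compared between arms by PERMANOVA "with alpha set at 0.05". The second of the Secondary Outcomes is "Persistence of resistome changes during the washout phase", judged against both baseline and the intervention period.

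The section Statistical methods for primary and secondary outcomes then says: "Statistical comparisons between groups and across time points will be performed". It names these methods:

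- For prevalence between groups, a suitable parametric or non-parametric test, chosen by the data distribution.
- For composition, PERMANOVA, with no statement of how permutations are made.
- For means: "Comparison of means will be done using an unpaired t-test", together with Tukey's test, with a qualifier that they apply where suitable.

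No paired test, change-score analysis, repeated-measures model or participant-restricted permutation is named anywhere in the protocol.

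**The concern.** A comparison of week 2 with baseline in one arm uses two values from each of the same 12 people. People differ in which resistance genes they carry, so the two values are likely to be positively correlated. An unpaired t-test, or Tukey's test over the three visits, puts the stable between-person variation into the error term, although it cancels from the within-person difference. Freely permuted PERMANOVA across visits does the same.

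The before/after and persistence comparisons are at stake. With 12 people per arm there is little power to give away. Persistence is especially exposed: a weak test may fail to separate washout from baseline when a change has lasted. It may equally fail to separate washout from week 2 when the change has faded, and that result is easily misread as persistence.

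**Working it through.** **The plan's own figure.** The 36 participants cannot be reproduced from a calculation, because Sample Size gives no effect size, SD or power. For orientation, by the normal approximation 12 per arm gives 80% power between two arms at a difference of about 1.15 SD.

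**Inputs from the protocol.** n = 12 per arm; 3 samples per person, so 36 × 3 = 108 samples; alpha 0.05.

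**Assumptions, because the protocol gives no values.** Two-sided test; normal outcome with SD 1; the same within-person correlation ρ between any two visits, varied over a range; true change of 0.8 SD.

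**Step 1: standard error of a before/after difference.** The true value is √[2(1 − ρ)/n]. The unpaired test estimates √(2/n) = √(2/12) = 0.408 whatever ρ is. The true values are 0.342, 0.289 and 0.224 at ρ = 0.3, 0.5 and 0.7. The unpaired standard error is therefore too large by a factor 1/√(1 − ρ), which is 1.20, 1.41 and 1.83.

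**Step 2: paired power from the noncentral t distribution.** There are 11 degrees of freedom, the critical value is 2.201, and the noncentrality is 0.8/√[2(1 − ρ)/12] = 2.342, 2.771 and 3.578. Power is 57.0%, 71.4% and 90.2%.

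**Step 3: both tests by simulation** (40,000 data sets per correlation).

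| ρ | Type I error, unpaired | Type I error, paired | Power, unpaired | Power, paired |
|---|---|---|---|---|
| 0 | 4.9% | 4.8% | 46.2% | 42.8% |
| 0.3 | 2.2% | 4.9% | 46.2% | 56.8% |
| 0.5 | 0.9% | 4.9% | 45.7% | 71.5% |
| 0.7 | 0.2% | 4.9% | 45.5% | 90.3% |

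The paired column agrees with step 2. With no correlation the unpaired test is slightly better, because it has 22 degrees of freedom instead of 11.

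**Step 4: PERMANOVA across time in one arm** (12 binary genes, the panel size in Antimicrobial Resistance Gene Detection; assumed prevalence 50%; 600 simulated trials, 199 permutations each). With free permutation, type I error is 0.3% at latent ρ = 0.5 and 0.0% at 0.7. With permutations restricted within participant it is 5.0% and 3.8%.

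**Step 5: between arms, one value per person.** The unpaired t-test has type I error of 5.0% to 5.1% for ρ from 0.3 to 0.9, both at one visit and on the change score. PERMANOVA at one visit gives 4.8% and 3.8% at ρ = 0.5 and 0.7. The named tests are sound here.

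**Step 6: between arms, if all three visits were pooled as independent samples** (36 against 36). At ρ = 0.3, 0.5 and 0.7 the unpaired t-test has type I error of 12%, 17% and 21%, and Tukey's familywise error is 16%, 23% and 30%. Freely permuted PERMANOVA on 108 samples gives about 55% at 0.5 and 80% at 0.7. The protocol does not describe this analysis; the figures only show why it should be ruled out.

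**The case against.** The strongest defence is that the unpaired t-test, Tukey and PERMANOVA are ordinary tools for comparing independent arms, and that the primary comparison is between arms. Read as one value or one change score per person, they hold their error rate (step 5). The text does not explicitly attach the t-test to before/after comparisons, and it adds a qualifier about suitability. A statistical analysis plan could supply the rest. Much of this stands: the between-arm primary comparison is not shown to be wrong, and the permutation scheme for PERMANOVA is detail that such a plan could properly settle.

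It does not remove the point. Comparisons across time are planned in the same section, and the only tests named there for means are unpaired. The suitability qualifier selects from a list with no paired option. The open choice of test covers prevalence between groups, not change over time. An analysis plan that followed the protocol's wording would carry the unpaired test forward.

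Three stronger readings are tempting but not supported:

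- A reader might infer that false positives are built into the between-group tests. They need pooling of visits, which is neither stated nor excluded. Prevalence is to be calculated at each phase separately, and the primary outcome stops at week 2.
- A reader might infer that every reported p-value must be wrong. Step 5 shows otherwise.
- A reader might infer that a t-test is prescribed for binary gene results. Prevalence has its own sentence, and a mean could be a per-person gene count.

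**Conclusion.** The point holds for comparisons across time. As written, the named unpaired tests give conservative, underpowered p-values for the before/after and washout-persistence comparisons. At an assumed 0.8 SD change with 12 people, power stays near 46% where a paired test would reach 57% to 90% for correlations of 0.3 to 0.7, and the nominal 5% error becomes 2.2% down to 0.2%. These sizes depend on the assumed effect and correlation. The direction holds for type I error at any positive correlation; the power loss needs enough correlation to outweigh the degrees of freedom lost by pairing, and is clear from 0.3 upwards. The error does not by itself produce false claims of benefit, and it does not invalidate between-arm tests that use one value per person.

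**What to change.** Revise the sentence on comparison of means and state how participants enter each analysis:

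- **Between arms:** confine the unpaired t-test, Tukey and freely permuted PERMANOVA to one value per person. For the primary outcome, use the baseline-to-week-2 change or a baseline-adjusted week-2 value. State that visits will not be pooled as independent samples.
- **Across time:** use a paired test or a mixed model with a participant effect for gene counts, exact McNemar for presence or absence of each gene, and PERMANOVA with permutations restricted within participant.
- **Conclusions:** base effect and persistence on the difference in change against control, at week 2 and at washout. A within-arm p-value alone should not carry either.

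The cost is wording only. No extra participants, samples or visits are needed, and it should be settled before the data are analysed.
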